### Sample size

A minimum of 500 gold-standard positive and negative participants for each cancer type are selected to obtain confidence interval width of <0.1 for sensitivities and specificities >0.80 across all survey modalities. A total study sample size of at least 1,576 individuals will contribute information to validity analyses of cancer screening history (Fig 1). For subgroups representing 20% (n = 100) of each cancer screening cohort, highly concordant screening tests (>0.9) and tests with good concordance (>0.8) will have 95% confidence interval widths of <0.12 and <0.16 respectively. We estimate that 1,260 (80%) participants would need to be included for the assessment of test-retest reliability across all screening modalities, resulting in >0.80 power to rule out Kappa coefficients smaller than 0.61 if the true test-retest agreement is greater than 70%.

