#### Reliability analyses

In contrast to validity, reliability analyses have a relatively simpler task in answering the following question: are the reports of screening behavior on an initial survey congruent with a follow-up survey regardless of the accuracy of the behavior with respect to EMR data?

Test-retest reliability, the reproducibility of a measure [40], will be assessed for each type of cancer screening. We will code a participant’s responses as consistent if the time interval between the survey date and the self-reported month and year was within guidelines on both the validation and reliability surveys, or if no test within guidelines was reported on both surveys. Patients with a screening test documented in the EMR for a given cancer site between completion of the validity and reliability surveys, or who were up to date with screening at the time of the validity survey but not at the time of the reliability survey due to the passage of time, will be excluded from reliability analyses due to the possibility that their true cancer screening status may have changed.By cancer type and survey modality, we will use Cohen’s Kappa [41] statistic to assess repeatability while correcting for chance agreement between survey administration time points. Kappa coefficients >0.80 are often used to indicate *excellent* agreement while *Kappa* coefficients between 0.61 and 0.80 indicate *substantial* agreement [42]. For participants whose screening status changes during the period between the baseline and follow-up surveys (e.g., due to recently being screened), response concordance will be measured against the updated screening status. As with the validity analyses, we will also analyze reliability by the time of the last recorded screening examination in groups, such as within 6 months, 6 months to less than a year, etc., as well as by questionnaire modality (web vs. phone). That is, we will see if the reliability coefficients for an answer to recent screening depend on the length of time to the last screening examination.

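### The reliability power statement is wrong as written: 70% raw agreement caps kappa at 0.45, and reading it as kappa 0.70 secures the stated power only for the pooled 1,260, not for the kappas planned by cancer and mode

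*Protocol article*

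**What the plan says.** The Sample size section of the protocol article gives one power figure; its other precision targets are confidence interval widths. It first sets the retest number: "We estimate that 1,260 (80%) participants would need to be included for the assessment of test-retest reliability across all screening modalities". The power that it claims for this number is then worded as "resulting in >0.80 power to rule out Kappa coefficients smaller than 0.61 if the true test-retest agreement is greater than 70" percent. The base is the validity sample: "A total study sample size of at least 1,576 individuals will contribute information to validity analyses of cancer screening history".

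For the size of each cancer cohort the same section says "A minimum of 500 gold-standard positive and negative participants for each cancer type are selected to obtain confidence interval width of <0.1", and then refers to precision "For subgroups representing 20% (n = 100) of each cancer screening cohort".

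The Reliability analyses section codes each participant as consistent or not on a yes/no item (a test within guidelines on both surveys, or on neither). It assesses test-retest reliability for each type of cancer screening and fixes the unit of analysis: "By cancer type and survey modality, we will use Cohen’s Kappa". It treats 0.61 to 0.80 as the band of substantial agreement. It also states that participants screened between the two surveys, or no longer up to date by the second, "will be excluded from reliability analyses due to the possibility that their true cancer screening status may have changed".

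**The concern.** The sentence sets a bound on one scale (kappa, 0.61) against a true value on what reads as another (agreement, 70%). Kappa corrects for chance and raw agreement does not, so on a yes/no item the first is normally well below the second. If 70% is raw agreement, the true kappa lies inside the region that the study is meant to exclude.

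The power is also attached to 1,260 people in total, while the kappas to be reported are for single cancers and for modes within them. The retest sample size rests on this sentence. A reader who takes it at face value will misjudge both the agreement needed to exclude 0.61 and the precision of the reported kappas.

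**Working it through.** **Inputs.** From Sample size: 1,576 validity participants; 1,260 retests (1,260/1,576 = 0.80); kappa bound 0.61; 70%; power above 0.80; 20% of a cancer cohort = 100, hence 100/0.20 = 500 per cancer. Assumed because not stated: 5% level, one- or two-sided test, prevalence of 50% (33% or 67% as the alternative), 1:1 mode split. Power pairs below are one-sided / two-sided.

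**1. 70% as raw agreement.** Kappa = (po − pe)/(1 − pe).
- Balanced margins: pe = 0.50, so kappa = (0.70 − 0.50)/0.50 = 0.40.
- Most favourable margins (0.35 on one survey, 0.65 on the other): pe = 2 × 0.35 × 0.65 = 0.455, so kappa = 0.245/0.545 = 0.4495. A grid over all margins gives the same maximum.
- Equal margins at 33% prevalence give 0.32.
- Kappa of 0.61 needs raw agreement of about 0.80 at the most favourable margins and 0.805 at balanced margins: (0.805 − 0.50)/0.50 = 0.61.

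At 70% raw agreement the true kappa is therefore below 0.61, and power to exclude values below 0.61 is essentially zero at any n.

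**2. 70% as kappa 0.70: the plan's own figure.** At balanced margins kappa 0.70 means raw agreement of 0.50 + 0.70 × 0.50 = 0.85. The large-sample variance of kappa for a binary item with equal margins is V/n, with V = 0.51 at kappa 0.70 and 50% prevalence, and V = 0.581 at 33% or 67%. Power = Φ(0.09/SE − z), with z = 1.645 or 1.96.
- n = 1,260: SE = √(0.51/1,260) = 0.0201; 0.09/SE = 4.47; power 0.998 / 0.994.

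The stated figure is met for the pooled sample.

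**3. Kappa 0.70 at the level of the planned analysis.**

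| Unit | n | 50% prevalence | 33% or 67% prevalence |
|---|---|---|---|
| One cancer, 80% of 500 | 400 | 0.81 / 0.71 | 0.76 / 0.66 |
| One cancer and mode | 200 | 0.55 / 0.43 | 0.51 / 0.39 |

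At n = 400, SE = 0.714/20 = 0.0357 and 0.09/SE = 2.52, giving Φ(0.875) = 0.81 and Φ(0.56) = 0.71. At n = 200, SE = 0.0505 and 0.09/SE = 1.78. Simulation with 20,000 runs at 50% prevalence gave 0.78 / 0.69 for n = 400 and 0.54 / 0.45 for n = 200. One kappa needs 390 people one-sided or 495 two-sided for 0.80 power at 50% prevalence, and 444 or 564 at 33%.

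**4. Exclusions.** No rate is given. At 50% prevalence, an assumed 10% loss (n = 360, SE = 0.0376) gives 0.77 / 0.67, and an assumed 20% loss (n = 320, SE = 0.0399) gives 0.73 / 0.62.

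**5. If cohorts were 1,000 per cancer** (500 positive plus 500 negative): 800 retests per cancer give 0.97 / 0.95 and a cancer-by-mode cell of 400 gives 0.81 / 0.71, both at 50% prevalence. The 500 reading fits the text better. It follows from the 20% = 100 figure, and 250 positives or 250 negatives at 0.80 give an interval width of 2 × 1.96 × √(0.16/250) = 0.099, just inside the stated 0.1.

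**The case against.** The article uses the word agreement in two senses. The section on primary validity analyses glosses Cohen's kappa as a level of agreement and also uses percentage agreement for concordance. Kappa 0.70 is thus an allowable reading, and it is the one that makes the sentence coherent. On that reading the figure holds comfortably for the 1,260 it names. This stands, and it limits the charge of an unattainable power to the raw-agreement reading.

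A reader might infer that the power statement cannot be true on any reading, or that it holds only for one cancer's cohort tested one-sided. Neither follows, because the pooled sample gives about 0.99. A reader might also infer that the plan promises 0.80 power for every cancer-by-mode kappa. It does not: the Sample size section makes no such promise, and the Reliability analyses section uses 0.61 and 0.80 as descriptive labels without stating a test. The shortfall there is a mismatch between two sections and does not make the sentence false.

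Two further cautions stand. Cell sizes are derived, since Fig 1 is not shown and the minimum of 500 is ambiguously worded. The loss to exclusions is also unsettled, because the same section says elsewhere that responses of people whose status changes will be judged against the updated status.

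The objection does not remove the point. The sentence writes kappa as a decimal and agreement as a percentage, so raw agreement is its natural reading. No kappa pooled over cancers is planned either. Reading the phrase on cancer type and modality as two separate breakdowns gives about 630 per mode and 0.94 / 0.89, but that pools cancers, whereas the section assesses reliability for each one.

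**Conclusion.** The concern holds in this form. Read as raw agreement, which is how it is written, the sentence is wrong: kappa is at most 0.45 at 70% agreement, and no sample size gives power to exclude values below 0.61. Read as kappa 0.70, it is right for the pooled 1,260, but that is not the level at which kappa will be reported. For one cancer, the claimed power is reached only with a one-sided test, prevalence near 50% and almost no exclusions. For one cancer and mode, it is about 0.55 one-sided or 0.43 two-sided.

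The kappa ceiling needs no assumption beyond a two-category outcome. The per-cancer and per-cell figures rest on 500 per cancer, 80% retest, a 5% level, the stated prevalences and, for cells, a 1:1 mode split. With 1,000 per cancer the per-cancer power would be adequate and a cell would reach 0.81 / 0.71. Nothing here shows that more participants are required, and the validity sample size, which rests on interval widths, is not affected.

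**What to change.** In the Sample size section, replace the 70% agreement with a true kappa of 0.70 and give the matching raw agreement (85% at 50% prevalence). Restate the power per cancer on the number expected after the exclusions in the Reliability analyses section, naming the sidedness and the assumed prevalence. State that the cancer-by-mode kappas are descriptive and will be reported with confidence intervals. The change is text only and adds no participants. Its cost is a less favourable stated power, about 0.7 to 0.8 per cancer at 50% prevalence before exclusions.

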**Fig 1 pone.0297773.g001:**
[figure not shown]
Design for overall and interview mode sub-study.

### Instruments/Measures

We conducted systematic cognitive interviewing of colorectal, breast, cervical, and lung cancer screening questions from the 2021 National Health Interview Survey in both English and Spanish to ensure these questions were well-understood by our populations (S1 Appendix). We performed one sub study on cervical cancer at the UW and University of Texas Southwestern and this was analyzed separately [33]. Both web- and phone-based validity surveys included eligibility questions, demographic questions, and cancer screening questions. This led to several important changes to the NHIS questions. Through cognitive testing we learned that some participants had challenges determining the main reason for their most recent exam. The question was initially a single question that included multiple options that participants could choose as the main reason for their most recent exam, such as “routine,” “follow-up to a recent exam,” or “because of a problem.” When given the option, respondents generally did not want to choose only one answer to this question. To improve the ability to answer the intent of this single question, we created a three-question series where we separated each reason into an individual question with dichotomized yes/no options. Additionally, we found that exams with similar procedures were confusing for some participants; therefore, we added additional details to help improve the clarity of the exams. For example, some participants in the cognitive surveys had challenges distinguishing between colonoscopy and sigmoidoscopy exams; therefore, we separated the questions about these exams and added more details about the exam procedures. Similarly, we added explanatory information for the Cologuard test, which participants had challenges distinguishing from the blood stool FIT test. We included more specifics to explain the differences in sample collection process of both exams. We performed a second round of cognitive testing and found our modification of the questions improved participants’ understanding of questions included in the survey.

### Recruitment and data collection

Each site is responsible for the recruitment and interviewing of participants from their healthcare system. As described above, each site regularly sends samples of eligible participants to the UW DCC for stratified selection and randomization. The UW DCC returns a list of randomized study participants back to each site. Staff from each site mails recruitment and study information letters to these potential participants. The recruitment letters include information on their assignment to either the phone or web survey. If assigned to the web survey, the recruitment letters include a survey link and QR code along with a unique study ID in two parts (ID and PIN). If assigned to the phone survey, potential participants are notified in the letter that a member of the study team would be calling them to conduct their interviews. Trained interviewers call participants one week after the letters are sent. Participants are called up to 5 times if they do not complete the survey online or are unavailable by phone. For each group, we offer the option to complete the survey via an alternate modality for participants who ask for this option (i.e., phone participants are emailed a web link if they preferred to complete it online and web participants are offered the opportunity to do the survey over the phone).

Invited participants complete eligibility questions and if eligible, respond to the cancer screening questions. The cancer screening survey questions include questions on whether the participant had received cancer screening exams, when they received their most recent cancer screening exam, the type of exam they received, and the main reason for their most recent screening exam. Participants are asked the most important reason for not being screened if the participant has not recently received a cancer screening or is not up to date with the specific type of cancer screening.

For reliability, staff from each site are mailed a second letter to participants either 1- or 3-month(s) after they complete the initial survey, if they complete at least one cancer screening question on the initial survey. Trained interviewers conduct follow-up in the same manner as the initial survey. Participants are asked to complete the same survey questions they complete in the initial survey, using the same modality (phone or web) they use for their initial survey. We send reminders to improve the response rate. We mail participants cash incentives for completing the validity ($10) and reliability ($15) surveys.

### Validation

To test the validity of the cancer screening questions, we will compare participants’ survey responses to gold standard EMR data. Not all questions on the survey can be validated. For example, we cannot validate questions about whether the doctor explained the exams at the visit or about the cost of procedures. In these cases, either the information is not recorded, or not available in EMR data.

To make these comparisons, we will obtain EMR data (e.g., utilization data on procedure and diagnosis codes) before each person’s survey. UW, KPWA, MHS, and HFH have extensive automated healthcare utilization data, which include enrollment (for KPWA) and demographics, diagnoses, procedures, outside claims, and cancer diagnoses. Electronic data are available for the entire study period and are housed in enterprise data warehouses at each site where they are readily available to programmers. Within these health systems, we can accurately identify whether each person sad any prior exams in the past five years with their results, dates, types of exams, and indication. We have used EMR data in many previous studies at KPWA and similar institutions to identify cancer screening tests [34–36]. As an insurer, KPWA also obtains claims for procedures that occur at non-KPWA facilities. For the purposes of assessing validity, these data will be considered the gold standard with which to compare self-reported responses on each screening questionnaire. The focus of the questions for validation are the ones for each cancer site that directly measure the outcomes for the Healthy People objectives. Our analysis of questions and their validity will focus on what the specific screening examination was, when was the last exam, and the main reason for the exam.

### Statistical analyses

#### Primary aims and analyses on validity

For each cancer site, as well as for groups of related questions, we will construct a misclassification matrix for each question from the screening history questionnaires, by cancer site and question group (related questions) (Table 3). All variables will be dichotomous (prior exam in the last 5 years [yes/no], exam type [e.g., co-test, primary HPV, Pap; colonoscopy yes/no], indication [screening yes/no]) or can be dichotomized (screening interval [e.g., </> recommended screening interval]). To correctly characterize agreement, we will need to ensure the tests from the medical records are classified as screening or diagnostic. In some cases, standard codes are available. In other cases, the time interval between exams from the EMR may be helpful in evaluating whether tests received were intended for screening or diagnostic evaluation. We will adopt the approach taken by Vernon, et al. (2008), and focus on measures of concordance, including sensitivity, specificity, reports to records ratio, positive and negative predictive values (PPV and NPV), and Cohen’s Kappa (level of agreement) [15]. Specifically, we will evaluate:

Sensitivity (probability of self-reported screening test when a test was received)Specificity (probability of no self-reported screening test when no test was received)Overall concordance (percentage agreement)Reports to records ratio (percentage of self-reported screening tests divided by percentage of records with a screening test; a ratio >1.0 indicates over-reporting, and <1.0 indicates under-reporting)PPV: the proportion of truly having been screened when self-reported screening.NPV: the proportion of no screening test when no self-reported screening.

**Table 3 pone.0297773.t003:** Misclassification matrix for dichotomous (or derived dichotomous) question outcomes.

	Electronic Health Record Gold Standard		
Self-Reported Survey	Outcome present	Outcome absent	
Outcome identified	A (true positives)	B (false positives)	PPV = A/(A+B)
Outcome not identified	C (false negatives)	D (true negatives)	NPV = D/(C+D)
	Sensitivity = A/(A+C)	Specificity = D/(B+D)	Concordance = (A+D)/(A+B+C+D); Reports to records = (A+B)/(A+C)

For sensitivity, specificity, PPV, NPV, and concordance we will calculate 95% confidence intervals based upon the binomial distribution. Sensitivity and specificity indicate the effectiveness of a test (here the NHIS survey result) with respect to a trusted “outside” referent, while PPV and NPV indicate the effectiveness of a test (the NHIS survey result) for categorizing people as having or not having a target condition/screening [37].

We will also calculate the report-to-records ratio, the ratio of participants reporting a test (true positives plus false positives) divided by the percentage of tests in the record (true positives plus false negatives). The report-to-records ratio is a measure of net bias in test reporting, where values >1.0 denote overreporting and values <1.0 denote underreporting [38]. All measures will be calculated for each cancer screening test type, as well as by mode of survey administration. For reports to records ratio, 95% confidence intervals will be generated using bootstrap resampling [39].

In our analysis, we will compare our accuracy measures for those completing the survey by web vs. phone. Because survey modality (phone vs. web) was randomly allocated, and we allow participants to change their mode of completion when we contact them, we will perform both an intent-to-treat analysis as well as a separate analysis by modality used.

For responses to the question ‘when did you have your most recent test to check for [cervical/breast/colorectal/lung] cancer’, we hypothesize response accuracy will vary based on the length of time since the last screening exam. We will present the proportion of patients who answer ‘yes’ to having had screening stratified by ranges of time between the survey date and time of last screening exam, including a stratum for those who have not had this exam within the study reporting period of 5 years. In addition, we will present the proportion of patients who had screening exams, within these ranges of time, among those who answer ’yes’ or ’no’ to each question. All analyses will be stratified by cancer site.

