### Stratification and randomization

We extract data on prior cancer screening from EMRs using Common Procedural Terminology (CPT) codes, International Classification of Disease (ICD) codes, and home-grown codes from each health plan. Participants are stratified by screening status into three groups based on EMR data: up to date with screening based on USPSTF recommendations, screened in the past five years but not up to date with their screening, and eligible but not screened in the past five years. Participants are stratified by race and ethnicity with the goal of recruiting at least 25% Non-Hispanic Black participants and 25% Hispanic participants for the study population. If not enough available participants are available to recruit from a given stratum, we select additional participants from other strata. Random samples of eligible participants from each study site are sent to the UW Data Coordinating Center (UW DCC) for stratified randomization for initial survey modality (phone vs. web) and subsequent survey timing (1 vs 3 months) on a regular basis at KPWA, UW, and MHS. Due to administrative requirements at HFH, patients at this site ware randomly assigned to their survey modality but not their follow-up time. We select HFH patients for participation in two waves. Those selected in May 2023 were assigned to 3-month follow-up, whereas those selected in August 2023 were assigned to 1-month follow-up. To maximize study efficiency, we select people who are eligible for more than one screening exam based on EMR information. For example, we combine cervical and breast cancer screening questions for women ages 40–49 and breast, cervical, and colorectal cancer screening for women aged 50–65 (Table 2).

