### Limitations

We recognize that EMR data have flaws. For example, coding is sometimes done in billing departments, and thus, the indication for use of a particular test may have inaccuracies. In addition, some tests, such as colonoscopy, can present challenges, such as the finding of a pre-cancerous polyp changing what had been indicated as a screening examination to one that may be now coded as a diagnostic examination. Missing tests, such as those that may be sent to a patient’s home for stool sampling, will also occur. However, they represent the strongest evidence with which to compare self-reported data. We recognize the limitations associated with this electronic approach but acknowledge that this method is similar to what health systems use to calculate HEDIS performance [43].

Qualitative studies are essential for understanding the reasons for not participating in screening, which are not possible to verify with our study approach. As an additional potential limitation, we note that the population included in the survey may not capture information about people of interest where information would be helpful to plan interventions. There might be other risk factors that prevent people from utilizing screening tests, such as lower health literacy, which is hard to measure, yet could interfere with patients’ study enrollment response. Hiatt et al. (2002) note sociodemographic correlates, health care system correlates, knowledge/behavioral/attitudinal correlates, health status/health profile correlates could have an impact on agreement indices, none of which we will be able to evaluate [10]. Although we are able to conduct interviews in Spanish, there will be too few in this study to perform separate analyses to determine the influence of language on screening understanding and recall. Other languages will not be attempted, but the results of this study would continue to establish a current baseline on concordance to serve as a reference for other investigators. We are aware that the prevalence of cancer screening uptake in the population may impact sensitivity and specificity. Thus, comparing those indices across cancer screening modalities with substantial uptake discrepancies may cause challenges.

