It is also likely that those who have never been screened may well be less likely to join a study like ours. This would result in an incorrect estimate in screening from surveys that we would not specifically address with these type of validity studies. However, we can estimate response rates by screening status to determine whether or not this is the case in our study.

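### PPV, NPV, concordance, report-to-records ratio and kappa are taken from unweighted cells of a sample selected on the gold standard, so they depend on the sampling mix and not on source-population uptake

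*Protocol article*

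**What the plan says.** Under Stratification and randomization: "Participants are stratified by screening status into three groups based on EMR data". The groups are up to date, screened within five years but not up to date, and not screened within five years. A second layer concerns race and ethnicity, "with the goal of recruiting at least 25% Non-Hispanic Black participants and 25% Hispanic participants". Shortfalls are refilled: "If not enough available participants are available to recruit from a given stratum, we select additional participants from other strata". Under Sample size: "A minimum of 500 gold-standard positive and negative participants for each cancer type are selected".

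The Validation section makes EMR data the gold standard. Table 3 gives each index as a raw-cell formula: PPV is A/(A+B), NPV is D/(C+D), and for the other two "Concordance = (A+D)/(A+B+C+D); Reports to records = (A+B)/(A+C". The list of validity measures also includes "positive and negative predictive values (PPV and NPV), and Cohen’s Kappa (level of agreement"). Intervals are simple binomial, with a bootstrap for the ratio. The ratio is read as net bias: above 1 is over-reporting, below 1 under-reporting. The Discussion makes the degree of over-reporting one of the study's outputs.

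The only remark on prevalence, under Limitations, is that "the prevalence of cancer screening uptake in the population may impact sensitivity and specificity". On non-response by screening status, the authors add that "we can estimate response rates by screening status".

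**The concern.** When people are selected on the gold standard, the column totals A+C and B+D no longer reflect how common screening is in the source population. Sensitivity and specificity condition on a column and largely survive this. PPV, NPV, concordance, the ratio and kappa combine the two columns, so they take on whatever mix the sampling produced. The protocol fixes both the selection and the unweighted formulas, and then interprets the ratio as a statement about reporting bias. A reader would take the published ratio and PPV as properties of the questions in these health systems and compare them with Table 1, where prevalences differ. The caveat under Limitations is attached to the two measures least affected.

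Sensitivity and specificity are not fully protected either. With three strata, a question on being up to date pools two negative groups (lapsed, and unscreened for five years), and a question on any exam in five years pools two positive groups. The protocol itself expects accuracy to vary with time since the last exam, so the pooled value shifts with the stratum mix.

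**Working it through.** **Inputs.** Sensitivity (Se) and specificity (Sp) come from Table 1 where a row exists. p is the share of gold-standard positives in the analysed sample. The documents give no screening prevalence for the four systems, so source values of p are assumptions. The 50:50 sample reads the target of 500 as 500 positives and 500 negatives.

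**Formulas**, from Table 3 with A = p·Se, C = p(1−Se), B = (1−p)(1−Sp), D = (1−p)Sp:

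- ratio = Se + (1−Sp)(1−p)/p
- PPV = p·Se / [p·Se + (1−p)(1−Sp)]
- NPV = (1−p)Sp / [(1−p)Sp + p(1−Se)]
- concordance = p·Se + (1−p)Sp
- kappa = (concordance − e)/(1 − e), where e = p·q + (1−p)(1−q) and q = A + B
- the ratio equals 1 at p = (1−Sp)/[(1−Sp) + (1−Se)]

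**Check against the documents' own figures.** The Ontario mammography row has Se 0.96, Sp 0.64 and ratio 1.18. Solving 1.18 = 0.96 + 0.36(1−p)/p gives p = 0.36/0.58 = 0.621. That p gives PPV 0.596/(0.596 + 0.136) = 0.81, against 0.821 in the table, so the formulas reproduce the row to rounding.

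**Results**

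| Case | p | Ratio | PPV | NPV | Concordance | Kappa |
|---|---|---|---|---|---|---|
| Mammography, 0.96/0.64 | 0.50 | 1.32 | 0.73 | 0.94 | 0.80 | 0.60 |
| same | 0.621 (study's own) | 1.18 | 0.81 | 0.91 | 0.84 | 0.64 |
| same | 0.75 (assumed) | 1.08 | 0.89 | 0.84 | 0.88 | 0.65 |
| Lung, 0.80/0.90 (assumed) | 0.50 | 0.90 | 0.89 | 0.82 | 0.85 | 0.70 |
| same | 0.30 (assumed) | 1.03 | 0.77 | 0.91 | 0.87 | 0.69 |
| same | 0.20 (assumed) | 1.20 | 0.67 | 0.95 | 0.88 | 0.65 |
| same | 0.10 (assumed) | 1.70 | 0.47 | 0.98 | 0.89 | 0.53 |

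In counts, the lung case with 500 positives and 500 negatives has A = 400, C = 100, B = 50, D = 450, and a raw ratio of 450/500 = 0.90. Reweighted to 10% uptake per 1,000 people, A = 80, C = 20, B = 90, D = 810, and the ratio is 170/100 = 1.70. The ratio crosses 1 at 0.10/(0.10 + 0.20) = 1/3, so the reading reverses for any source uptake below one third.

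Whenever Se = Sp, a 50:50 sample returns a ratio of exactly 1.00, whatever the net bias in the source population.

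**Pooled strata.** If w is the share of lapsed people among sampled negatives, specificity for being up to date is w·Sp(lapsed) + (1−w)·Sp(unscreened). It is free of w only if the two specificities are equal.

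**The case against.** A reader might infer that the FOBT result must reverse. The Appalachian Ohio row (0.32/0.93, ratio 1.87) gives 0.39 if p is set to 0.50. The design does not support this. Strata and targets are per cancer type, and Table 2 counts colorectal screening as up to date by FOBT or FIT in one year or by endoscopy in five. In the same study, the tabulated ratios imply prevalences of 47.3% for colonoscopy, 4.3% for FOBT and 0.9% for sigmoidoscopy, so any-test prevalence lies between about 47% and 53%. If sampling acts only through colorectal status, a 50:50 sample leaves FOBT at 4.1 to 4.6% and the ratio at 1.95 to 1.78. Reversal would need sampled FOBT prevalence above 0.07/(0.07 + 0.68) = 9.3%.

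Other points also stand:

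- The mix is not fixed at 50:50. Short strata are refilled, many people are eligible for several screens, and the validation EMR data run up to the survey while the strata come from the data pull. This makes the mix unpredictable, not representative.
- The phone-versus-web comparison is not confounded, because both randomised arms share the mix.
- The planned tabulation of yes answers by time since the last exam, and the model of correct answers by actual status and recency, give useful stratum-level information. Neither reweights the pooled indices. The companion table, conditional on the answer given, has the same dependence on the mix.
- The aim is question validity, and over-reporting is only one output. Precision is planned for sensitivity, specificity and concordance. The ratio and PPV are nevertheless listed measures with a stated interpretation.
- Weighting could be left to an analysis plan that is not shown. Here, however, the article fixes raw-cell formulas and binomial intervals, so a plan that weighted would depart from it.

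**Conclusion.** The point holds. Followed as written, the plan reports PPV, NPV, concordance, the report-to-records ratio and kappa as functions of the sampled mix, not as estimates for the participating systems. The effect is clearest where a cancer has a single test. For mammography at Table 1's values, over-reporting is 32% at 50:50 against 8% at an assumed 75% uptake: same direction, different size. For lung, the direction can reverse if source uptake is below one third. That rests on assumed accuracy (0.80/0.90), because the protocol says no validation evidence exists for that test.

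Reversal is not general. It needs sample and source prevalence on opposite sides of the crossing point. For the mammography and Pap rows examined, that would take source uptake above about 0.84 to 0.94. Concordance is unaffected when sensitivity equals specificity. If the target of 500 means a total, the 50:50 figures change but selection on the gold standard remains. The documents also do not say that Henry Ford respondents' non-lung answers enter those cancers' primary estimates, so their inclusion is a possibility and not a demonstrated error.

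**What to change.** Keep the sampling and response fractions by site, recruitment category, EMR screening group and race/ethnicity. Report PPV, NPV, concordance, the ratio, kappa and any sensitivity or specificity pooled over strata, weighted to the eligible populations of the participating systems. Use design-based or stratified-bootstrap intervals, and show unweighted stratum-specific results beside them. The planned response rates by screening status can feed the weights.

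The protocol says sites send random samples to the coordinating centre and does not say that the centre holds full frame counts. These may have to be requested from the sites. If they cannot be obtained, report the indices at stated prevalences, with the range shown.

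Handle non-lung answers from lung-selected Henry Ford respondents through the site and recruitment weights, or with a sensitivity analysis without them. Rewrite the Limitations sentence so that the prevalence caveat names PPV, NPV, concordance, the ratio and kappa, and notes that pooled sensitivity and specificity depend on the stratum mix.

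The cost is wording, programming and perhaps a request for counts; no participants are added. Unequal weights will widen intervals somewhat, and the weighted figures describe the four health systems, not the nation.
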